## **PRÉCIS**

### **Study Title**

A cross-over study to compare efficacy and tolerability of brand versus generic alendronate in postmenopausal women with osteoporosis

### **Objectives**

Primary objective: Evaluation of difference in efficacy as measured by bone markers between brand versus generic alendronate in postmenopausal women with osteoporosis

Secondary objective: Evaluation of difference in tolerability between brand versus generic alendronate

### **Design and Outcomes**

A randomized single centre cross-over study to test the tolerability and efficacy of brand compared to generic alendronate in postmenopausal women with established osteoporosis.

Efficacy is evaluated by the assessment the bone resorption marker sCTx. It is hypothesised that there is no difference between brand versus generic alendronate

Tolerability is evaluated by the Gastrointestinal Symptom Rating Scale (GSRS) questionnaire and self-reported side-effects.

Medication use and adherence is evaluated by the Self-efficacy for Appropriate Medication Use (SEAMS) Questionnaire and the Brief Medication Questionnaire (BMQ).

### **Interventions and Duration**

After randomization, patients start with brand alendronate or generic oral alendronate once weekly in a single blinded, open label setting. After the first period of 12 weeks, there is a cross-over to generic and brand oral alendronate once weekly respectively. Evaluation of efficacy, tolerability and adherence is planned at week 4, 12, 16 and 24. After the study period of 24 weeks patients will continue treatment with the alendronate formulation they prefer, according to current guidelines.

### **Sample Size and Population**

30 postmenopausal women with a prior fracture and osteoporosis defined as a DEXA T-score  $\leq -2.5$  SD at one of the measured locations: lumbar spine, femoral neck or total hip.

## **1. Study objectives**

### **1.1 Primary Objective**

Evaluation of difference in efficacy as measured by bone markers between brand versus generic alendronate in postmenopausal women with osteoporosis

## **1.2 Secondary Objective**

Evaluation of difference in tolerability between brand versus generic alendronate in postmenopausal women with osteoporosis

## **2. BACKGROUND AND RATIONALE**

### **2.1 Background on Condition, Disease, or Other Primary Study Focus**

Osteoporosis is a progressive skeletal pathology characterized by loss of bone mass and quality and development of brittle bones that results in increased risk of fractures. The estimated worldwide number of new osteoporotic fractures for the year 2000 was 9.0 million, of which 1.6 million were at the hip, 1.7 million were at the distal forearm and 1.4 million were clinical vertebral fractures. In the Netherlands the number of osteoporotic fractures is estimated at 80.000 per year (RIVM). Osteoporotic fractures have extensive clinical and economic consequences, and are a major public health concern. The important burden of osteoporotic fractures highlights the need for osteoporosis therapies with established high efficacy. Treatment options for osteoporosis have substantially improved in recent years, appropriate antiresorptive or anabolic medications are available to prevent future fractures. At present, bisphosphonates are the most common therapy for osteoporosis.

Bisphosphonates inhibit osteoclast activity. Two chemically distinct groups of bisphosphonates exist: non-nitrogen-containing bisphosphonates (e.g. Etidronate) and nitrogen-containing bisphosphonates, (e.g. Ibandronate, Alendronate, Zoledronate, and Risedronate). There are two fundamentally distinct components of the mechanism of action of nitrogen-containing bisphosphonates (N-BPs). These are (1) binding to the bone, and (2) binding to and inhibition of a key osteoclast enzyme farnesyl pyrophosphate synthase (FPPS).

Bisphosphonates are today's worldwide leading medication. Regarding the oral bisphosphonates, only Risedronate and Alendronate have been proven to reduce vertebral and hip fracture risk in clinical trials. Zoledronate is an intravenous bisphosphonate therapy and has also been proven to reduce vertebral and hip fracture risk in clinical trials. According to the current Dutch guidelines (NHG standaard osteoporose 2005 and CBO richtlijn osteoporose 2002) alendronate and risedronate are the first-choice drugs for treatment of osteoporosis.

### **2.2 Study Rationale**

#### **2.2.1 Generic versus branded alendronate**

### 2.2.1.1 Scope

During the past years an increasing number of generic alendronates were introduced, in numerous countries. For generic drugs the EMEA/CBG guidelines require a bioequivalence study in which the pharmacokinetic profile of the brand formulation (i.e. alendronate) is compared to the reference generic product. Those studies are performed in healthy volunteers. Based on bioequivalence the generic product is expected to have the same clinical efficacy as the brand formulation. Insurances and Health Care Providers prefer physicians to prescribe mainly generic alendronate instead of branded original bisphosphonates like Fosamax® (Alendronate) or Actonel® (Risedronate). Little is known, however, about the provenience and quality of the generic Alendronates. Clinical trials or observational postmarketing studies on bone mineral density and fracture efficacy, adverse events and compliance or persistence with these new “Alendronic acids” initiatives were never performed. This is an important gap of knowledge and means that generic Alendronates are prescribed while it is not known whether efficacy and safety are really the same as was demonstrated for the original branded oral bisphosphonates in clinical or real practice studies. A major concern about the generic alendronates seems to be the reduced medication compliance in clinical practice. An additional issue is related to the poor oral absorption of bisphosphonates in the gastrointestinal tract: typically less than 1% is absorbed. The poor absorption of bisphosphonates is most likely due to their very poor lipophilicity and charge, which prevents transcellular transport across the epithelial barriers. The question arises whether the absorption of generic alendronates, and thus its bioavailability, is altered because of the variation in galenic/tablet properties. This can potentially affect the clinical outcome in terms of anti-fracture efficacy of this medication.

### 2.2.1.2 Literature overview

In-vitro studies have demonstrated important differences in disintegration en dissolution between Fosamax® and nine variations of alendronic acid. Epstein et al. showed a greater irritant response from a copy Alendronate tablet (Novo-Alendronate 10 mg) in a rabbit injection study and in a dog esophageal study (Alendronate Sodium Tablets, Teva Industries, Petah- Tikva, Israel) compared to the branded innovator product (Alendronate sodium tablets, 10 mg). The differences were attributed to the pharmaceutical preparation, since the active ingredient (Alendronate sodium) and the dose were similar between the copy Alendronate tablets and the branded tablets. The same authors also evaluated the disintegration and dissolution profiles of 13 copy Alendronate tablets available. From a safety perspective, the authors concluded that for the rapidly disintegrating formulations there is a chance that disintegration may occur in the mouth and/or the esophagus during swallowing of the tablet. This could increase the duration and extent of oral and esophageal tissue exposed to semi-particulate alendronate and thereby increase the risk of serious mucosal irritation and ulceration. From an efficacy perspective, Epstein et al. also concluded that tablets that disintegrate faster than branded Alendronate sodium tablets (1.4 min) could result in reduced efficacy because the premature disintegration may be associated with semi-particulate Alendronate being retained within the esophagus,

increasing the likelihood of contact with ingested food, saliva, mucus or liquids, thereby reducing the bioavailability or altering the pharmacokinetics. Generic Alendronate tablets with very short disintegration times start to disintegrate very quickly already in the mouth and esophagus. The already low intestinal absorption rates of these generic bisphosphonate drugs could be further decreased and full efficacy in terms of BMD increases not reached.

Two recent studies have shown differences in tablets' properties that might explain different rates of adverse events. An in vitro study compared the disintegration and dissolution of once weekly original branded Risedronate (Actonel®) and original branded Alendronate (Fosamax®) tablets with 26 different Generic Alendronate copies from Canada, Germany, the Netherlands, and UK. The mean disintegration times of the generic alendronate tablets in vitro ranged from 14 to 342 s (5.7 min). The mean disintegration time of the branded product tablets (Actonel® and Fosamax®) ranged only from 43 to 78 s. Six of the 26 companies market alendronic acid tablets having very rapid disintegration times which are similar to those of orally disintegrating tablets (non-bisphosphonates).

Another trial evaluated and compared esophageal transit times and in vivo disintegration of one branded risedronate and two generic formulations of alendronic acid tablets that are commercially available in Canada and the United Kingdom. It was shown that the two generic formulations of alendronic acid tablets had significant slower transit times than compared with the branded risedronate (Actonel®) tablet tested. Also a difference in adhesiveness of generic alendronate compared to Fosamax® has been postulated to contribute to this problem.

This is of importance for patients because delayed esophageal transit or disintegration of oral bisphosphonate tablets before they enter the stomach could cause iatrogenic complications. Different formulations of generic bisphosphonate tablets meeting regulatory requirements may have substantial differences in pharmaceutical attributes from the branded product that may result in different characteristics during esophageal transit.

It has been suggested that there are differences in persistence between different weekly oral bisphosphonate therapies, particularly a poor persistence for patients started on generic alendronate. In one study a higher incidence in gastro-intestinal side effects was reported in patients treated with generic alendronate as compared to those treated with original once weekly bisphosphonates. In a recently published paper the persistence of patients treated with generic alendronate was significantly lower as compared to those with branded alendronate. The total numbers of patients reporting gastrointestinal adverse events with generic alendronate was more than twice the number treated with Fosamax®. There was a significantly lower increase of lumbar spine and total hip BMD with generic alendronate compared to Fosamax®. The reasons for the 40–50% lower BMD increase rates when using the generic compound is not known yet. At least in part the lower efficacy can be explained by a significantly lower degree of persistence with generic alendronate, which could be related to a higher incidence of gastrointestinal side events. Other reasons could

be the lower bioavailability or potency of generic alendronate.

Based on these results it is postulated that rapid disintegration may enhance esophageal drug exposure leading to more gastro-intestinal side effects with a possible lower degree of persistence. On the other hand, longer disintegration times may result in altered, possibly delayed or impaired absorption of alendronic acid. Since absorption is less than 1% in branded alendronate there is concern about efficacy of generic formulations.

## **2.2.2 Surrogate parameters for evaluation of fracture risk reduction**

### **2.2.2.1 BMD**

In contrast to other generic medications like statins, anti-diabetic or anti-hypertensive drugs (where you can measure surrogate parameters for evaluation of cardiovascular risk in daily practice such as cholesterol, glucose, HbA1C, blood pressure) it is difficult to evaluate the anti-fracture efficacy of anti-osteoporotic drugs.

BMD as measured by DEXA is a tool developed by the WHO for evaluation of fracture risk and diagnosis of osteoporosis. With each SD decrease in BMD, the fracture risk doubles. The diagnosis osteoporosis is based on a BMD T-score  $\leq -2.5$ SD of the peak bone mass of healthy women between 20 and 30 years. A T-score between -1 and -2,5 is classified as osteopenia and a T-score  $\geq -1$  as normal. However, this technique is not developed and not useful for evaluation of fracture risk (reduction) during therapy, since the outcome (either increase or decrease of BMD) does not reflect anti-fracture efficacy on an individual basis. Furthermore, it takes at least 2 years to measure a true difference between 2 longitudinally BMD measurements due to the small gain during therapy (3-4% in two years for most drugs) in relation to the precision error of the technique (1-2%). In the Dutch guidelines (CBO 2002 and NHG 2005) it is recommended not to perform a BMD measurement for evaluation of therapy at all. It is advised to use this technique only for the diagnosis of osteoporosis and deciding whether to start treatment or not.

### **2.2.2.2 Bone turnover markers**

Current biological markers of bone turnover have proven useful in improving fracture risk assessment and monitoring treatment efficacy in postmenopausal osteoporosis. Bone turnover markers mainly reflect bone formation by osteoblasts and bone resorption by osteoclasts.

Osteoblasts synthesize collagen, bone-specific alkaline phosphatase (BALP) and osteocalcin. These parameters are therefore markers of bone formation. During synthesis of collagen the propeptides serum C-propeptide of type I collagen (PICP and PINP) are cleaved. These peptides can be measured in serum as a marker for collagen synthesis. During maturation of

osteoblasts in the skeleton, BALP is expressed. In serum the concentration of alkaline phosphatase is predominantly determined by liver- and bone isoenzyme fractions of alkaline phosphatase. Recent new techniques allow for measuring the bone-specific-isoenzyme (BALP) separately. Osteocalcin, is a small protein synthesized by osteoblasts during the late phase of the bone formation process. It contains three gamma-carboxyglutamine groups which enable a high affinity for calcium.

Bone parameters that reflect collagen degradation are the “collagen crosslinks” pyridinoline (PYD) and deoxypyridinoline (DPD) and the crosslinks with amino- and carboxyterminal telopeptides (NTx and CTx). These bone-markers are commercially available as immunoassay. Because of the natural biological variation within these parameters (diurnal rhythm), collection time is standardised at morning time. Furthermore the results have to be compared to a gender and age specific reference group preferably expressed in Z (or T) - scores. It is now known that high bone turnover is related to enhanced bone-loss in postmenopausal women and to increased fracture risk. It also has been shown that a decrease in bone-resorption markers predicts fracture-risk reduction in patients treated with anti-resorptive drugs. These aspects can be assessed by measuring bone-resorption markers like NTx and CTx (figure 1).

[figure not shown]

Figure 1: relationship between bone resorption markers expressed as a T-score and the 0- to 3-year incidence of new vertebral fractures. The placebo group is represented by the broken line and the risedronate 5 mg group by the solid line.

In contrast to BMD measurements, the alteration (decrease) in resorption markers occurs in the early phase during treatment. In fact, during the first 3 months of treatment with anti-resorptive medication such as bisphosphonates a decrease of 40-60% of bone turnover markers has been demonstrated (figure 2).

[figure not shown]

Figure 2: Changes in biochemical markers expressed as mean percentage change from baseline 

The predictive value of a decreased urine NTx for fracture risk reduction was 52%, significantly better than the predictive value of 14% with femoral neck BMD. 

At present, there can be no assurance that the Generic Alendronate tablets are equivalent to the branded product in terms of efficacy and tolerability. In order to gather more information with regard to efficacy and tolerability of branded compared to generic alendronate we designed this study in postmenopausal women with osteoporosis .

### **3. STUDY DESIGN**

- **Type/design of trial:** cross-over design
- **Primary outcome:**

Comparison of efficacy as measured bone -markers (serum CTx) between generic and brand alendronate formulations

With regard to the primary outcome we hypothesise that there is no difference between brand versus generic alendronate
- **Secondary outcome:**

Comparison of tolerability between brand and generic alendronate formulations
- **Study population and sample size:**

30 postmenopausal women with a prior fracture and osteoporosis, as diagnosed by DEXA (dual X-ray energy), with or without a previous fracture
- **Study location:**

out -patient, single-centre, VieCuri MC voor Noord-Limburg
- **Duration of screening period and follow-up:**

The screening period will be a maximum of 2 weeks

Intervention period: 24 weeks; i.e. 2 times (before and after cross-over) 12 weeks
- **Description of intervention and administration:**

After randomization, single blinded, open label administration of alendronate

15 patients start with generic alendronate and 15 patients with brand oral alendronate once weekly

After the first period of 12 weeks, cross-over to branded and generic oral alendronate once weekly respectively

Evaluation of side-effects, adherence and medication use (by questionnaires) and efficacy (by bone-markers) at day 1, week 4, 12, 16 and 24

After the study period of 24 weeks patients will continue treatment with the alendronate formulation they prefer, according to current practice.

#### **4. SELECTION AND ENROLLMENT OF PARTICIPANTS**

Patients will be selected at the out-patient fracture and osteoporosis clinic of the VieCuri MC Noord-Limburg. In this setting all patients are evaluated for possible metabolic bone disease because of a recent fracture by a questionnaire, DEXA and laboratory tests. Based on the results of these diagnostic tests decisions for further evaluation or treatment are made. Therapeutic intervention decisions are made according to the Dutch guidelines (CBO richtlijn osteoporose 2002 en NHG richtlijn osteoporose 2005) and patients are offered or advised to be treated with an oral bisphosphonaten in case of established osteoporosis. Patients who meet these treatment criteria will be asked by their physician (internist working at the VieCuri MC Noord-Limburg) to participate in this study. The study starts after informed consent has been signed by both patient and the principle investigator (Dr. [name]) with a screening on visit -1 .

##### **4.1 Inclusion Criteria**

- Ambulatory postmenopausal women, aged 50 years or older

(postmenopausal will be defined as no vaginal bleeding or spotting for at least 12 months)

Diagnosed with osteoporosis as defined by a DEXA measurement with a T-score of  $\leq -2.5$  SD at one of the measured locations: lumbar spine or femoral neck or total hip

- No treatment for osteoporosis in the 12 months before inclusion
- No fracture within the last 12 weeks
- Ability to understand study procedures and to comply with them for the entire length of the study.

##### **4.2 Exclusion Criteria**

- Patients with prior treatment of osteoporosis during the previous 12 months (bisphosphonates, testosterone, hormonereplacement therapy (HRT), selective estrogen receptor modulators (SERMs), or calcitonin)

- Vertebral or hip fracture within the last 6 months
- Patients who were previously intolerant of bisphosphonates
- Patients with disorders of esophageal motility or in whom oral bisphosphonates are contraindicated

A history of upper GI tract disorder other than esophageal motility disorder is not a reason for exclusion.

Note: prior or current use of nonsteroidal anti-inflammatory drugs (NSAIDs), proton pump inhibitors (PPIs), histamine (H2) receptor antagonists, aspirin, or glucocorticoids is not a reason for exclusion

- Participation of patients in a clinical trial
- Secondary osteoporosis: primary hyperparathyroidism, renal disease (MDRD < 30 ml/min), untreated primary hyper or hypothyroidism
- Not able to follow the drug and dose instructions
- Known malignancy within the last 5 years
- Alcohol use: > 4 units per day
- Inability or unwillingness of individual to give written informed consent

## **5. STUDY INTERVENTIONS**

Before subjects may be entered into the study, a copy of the site's written independent ethics committee/institutional review board (IEC/IRB) approval of the protocol, informed consent forms is required. All subjects must personally sign and date the consent form before enrollment.

### **5.1 Interventions, Administration, and Duration**

All patients will be treated in an out-patient setting with a commercially available EMEA approved formulation of alendronate for a total of 24 weeks; the brand formulation Fosamax® (manufactured by MSD) 70 mg for 12 weeks followed by a generic formulation (aledronic acid) 70 mg for 12 weeks ore vice versa in a cross-over setting. The medication will be administered by the pharmacist at the polytheek of VieCuri MC Noord-Limburg.

Both alendronate formulations must be taken once a week on the same weekday in the fasting

state with water at least 30 minutes before consuming food or beverages in a supine position.

The 70 mg dosage once a week of brand and generic alendronate is the current standard and registered dosage for the treatment of osteoporosis. During the study there will be no modification of the dose.

Side effects: The most common side effect of alendronate is stomach pain. It also may cause nausea, vomiting, bloating, constipation, diarrhea, gas, black stool (due to intestinal bleeding), change in taste perception, and muscle or joint pain. Alendronate may irritate the esophagus, causing ulcers and bleeding. This occurs more often when patients do not drink enough water with alendronate or don't wait 30 minutes before lying down.

A standard amount of 1000 mg Calcium and 800 U vitamin D will be added to the treatment with alendronate in all patients as Calci-chew D3 tablets once a day taken with the evening meal.

## **5.2 Handling of Study Interventions**

The study drugs will be delivered at the pharmacy 'polytheek' of the VieCui MC voor Noord-Limburg.

Randomization to generic versus brand alendronate at the start of the study will be performed by the site pharmacist by selecting previously prepared closed envelopes.

At delivery patients are explicitly instructed how to take the study medication. The amount of tablets exceeds the amount needed for the study period and patients are instructed to return the study medication at week 4, 12, 16 and 24 visit. At week 4, 12, 16 and 24 the number of returned tablets will be counted.

Calci-chew D3 is also delivered by the pharmacist at the polytheek.

## **5.3 Assessment of side-effects, adherence and medication use**

### **5.3.1 Side effects**

Gastrointestinal side effects are scored at base-line, week 4, 12, 16 and 24 by the Gastrointestinal Symptom Rating Scale (GSRS) questionnaire. The GSRS is a brief, fairly comprehensive assessment of common gastrointestinal symptoms based on 15 questions with regard to the previous 4 weeks before assessment. The GSRS has good reliability and construct validity. For detailed information see appendix 1.

Furthermore self reported side-effect will be monitored at baseline, week 4, 12, 16 and 24.

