## 6.2 Description of Evaluations

### 6.2.1 Study Visit Definitions

- The screening date is defined as the date the informed consent is signed.
- Enrolment date is defined as the date of randomization.
- Day 1 is defined as the day that brand or generic alendronate is dispensed to the subject.
- A study month is defined as a calendar month.
- Randomization must occur within 14 days of the screening and Day 1 must be completed within 72 hours of randomization.
- All on-study (post Day 1) visits should be scheduled from the initial Day 1 visit calendar date. For example, if a subject's Day 1 visit is January 15, then their Month-6 visit should be targeted to occur on July 15.
- If a subject's visit is delayed, their subsequent visit dates should not be shifted, but always calculated based on the Day 1 visit date.

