### 6.2.2 Study Visit Windows

All tests and procedures scheduled for Day 1 must occur within 72 hours of the randomization date.

All tests and procedures scheduled for the Week 4, 12, 16 and Week 24 visits must be performed within  $\pm 7$  days of the scheduled visit date.

Any missed visits, tests not done and examinations not conducted must be reported as such.

Study procedures for a specific visit may be completed on multiple days as long as all of the procedures are completed within the visit window.

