**Week 12 visit ( $\pm$  7 days)**

- Vital signs (including blood pressure and pulse)
- Physical Examination (including height and weight)
- Administration of GSRS, SEAMS and BMQ
- Laboratory samples
- Concomitant medication recording
- Adverse event collection
- Study drug accountability
- Brand or generic alendronate dispensed to subject (cross-over)

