## 8.5 Reporting Procedures

The investigator is responsible for ensuring that all adverse events (as defined in 8.1 and 8.2) observed by the investigator or reported by subjects are collected and recorded in the subjects' medical records. These adverse events will include the following:

The following adverse event attributes must be assigned by the investigator: adverse event diagnosis or syndrome(s) (if known, signs or symptoms if not known); event description (with detail appropriate to the event); dates of onset and resolution; severity; assessment of relatedness to investigational product and action taken.

If applicable, the relationship of the adverse event to the investigational product will be assessed by means of the question: "Is there a reasonable possibility that the event may have been caused by the investigational product?" The investigator should respond to this question with either Yes or No.

The severity grading scale used in this study is described in Appendix B.

Medically significant adverse events considered related to the investigational product by the investigator will be followed until resolved or considered stable.

It will be left to the investigator's clinical judgment to determine whether an adverse event is related and of sufficient severity to require the subject's removal from treatment or from the study. A subject may also voluntarily withdraw from treatment due to what he or she perceives as an intolerable adverse event. If either of these situations arises, the subject should be strongly encouraged to undergo an end-of-study assessment and be under medical supervision until symptoms cease or the condition becomes stable.

Procedures with regard to SUSARS (Suspected unexpected serious adverse reactions):

The investigator will report expedited the following SUSARs to the METC (Maastricht UMC) and CEM (Viecuri Venlo):

- SUSARs that have arisen in the clinical trial that was assessed by the METC and CEM;
- The remaining SUSARs are recorded in an overview list (line-listing) that will be submitted once every half year to the METC. This line-listing provides an overview of all SUSARs from the study medicine, accompanied by a brief report highlighting the main points of concern.

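### The week 16 GSRS falls exactly one recall period after the planned switch, so the visit windows let its 4-week recall reach back into the first formulation

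*Protocol*

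**What the plan says.** Tolerability is the secondary objective, and the GSRS is one of the two tools named for it in the Précis, next to self-reported side effects. Section 5.3.1 sets the times: "Gastrointestinal side effects are scored at base-line, week 4, 12, 16 and 24 by the Gastrointestinal Symptom Rating Scale (GSRS) questionnaire". The same section describes the questionnaire as "based on 15 questions with regard to the previous 4 weeks before assessment".

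The second formulation is handed out at the week 12 visit itself. Its list in 6.2.3 includes "Brand or generic alendronate dispensed to subject (cross-over)", and no washout is planned. The GSRS is next given at week 16.

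Two scheduling rules govern the dates. Section 6.2.2 begins "All tests and procedures scheduled for the Week 4, 12, 16 and Week 24 visits must be performed within" and allows 7 days either side of the scheduled date. Section 6.2.1 adds that if a visit is delayed, "their subsequent visit dates should not be shifted, but always calculated based on the Day 1 visit date".

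On drug supply, 5.2 says "The amount of tablets exceeds the amount needed for the study period" and asks women to bring their medication back at each visit. On dosing, 5.1 says "Both alendronate formulations must be taken once a week on the same weekday".

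The protocol sets no minimum interval between the actual switch and the week 16 GSRS.

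**The concern.** The recall period and the planned interval are both 4 weeks. On schedule, the week 16 GSRS covers the second formulation from the day of dispensing and nothing else. Any late switch, or any early week 16 visit, makes the recall longer than the time since the switch. The excess days belong to the first formulation, yet the score is filed under the second. A single answer about 28 days cannot be split afterwards.

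Week 16 is one of only two GSRS scores for the second formulation and the only one that covers its first weeks. If it is used to compare brand with generic, mixing the two exposures blurs that comparison. The trial was motivated partly by reports that the formulations differ in gastrointestinal side effects.

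**Working it through.** The protocol states no figure of its own here, so the check is date arithmetic.

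**Inputs** (days after Day 1)
- Week 12 visit and dispensing of the second formulation: 84 ± 7, so day 77 to 91 (6.2.2, 6.2.3).
- Week 16 visit with GSRS: 112 ± 7, so day 105 to 119. It is counted from Day 1 even when week 12 was late (6.2.1, 6.2.2).
- Recall: 28 days (5.3.1).

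**Formula.** Overlap = max(0, 28 − gap), where gap = week 16 day − week 12 day. The permitted gap runs from 105 − 91 = 14 to 119 − 77 = 42 days.

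**Per woman, counted from dispensing**

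| Week 12 shift | Week 16 shift | Gap | Overlap |
|---|---|---|---|
| 0 | 0 | 28 | 0 |
| +3 | 0 | 25 | 3 of 28 (11%) |
| +7 | 0 | 21 | 7 of 28 (25%) |
| 0 | −7 | 21 | 7 of 28 (25%) |
| +7 | −7 | 14 | 14 of 28 (50%) |
| +7 | +7 | 28 | 0 |

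A late week 12 visit under the no-shift rule accounts for at most 7 days. The other 7 come from the early edge of the ordinary week 16 window. If week 16 were counted from the switch but kept its ± 7 days, the maximum would still be 7.

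**For the group.** The protocol does not say how visits scatter within their windows, so this part rests on assumptions.
- Even, independent spread over whole days: there are 15 × 15 = 225 combinations. Some overlap occurs in 105 (47%) and 7 days or more in 36 (16%). In the other 69 of the 105 (31% of all combinations) it is 1 to 6 days. The full 14 days occurs in 1 of 225. The mean is 560/225 = 2.5 days, and 2.5/28 = 8.9%.
- Normal scatter with SD 2 days, cut off at 7: 43% have some overlap, 1% have 7 days or more, and the mean is 1.1 days, or 4.0%.

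**Effect on the contrast.** If every recall day counts equally and each formulation has a steady symptom level, the week 16 score is (1 − f) × second + f × first, with f = overlap/28. The difference from the first formulation is then multiplied by 1 − f. That is an average loss of about 4% to 9% at this visit, and 25% for a woman with 7 days of overlap.

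**Counting from the first tablet.** This is a different basis and should not be mixed with the figures above. With a fixed dosing weekday, the first new tablet may follow dispensing by 0 to 6 days. A woman exactly on schedule could then have 6 days before it (tablet on day 90, recall from day 84). The maximum is 28 − (105 − 97) = 20 days.

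**The other scores**
- Week 24: the recall starts no earlier than 161 − 28 = day 133, after the latest dispensing (day 91) and the latest first tablet (day 97).
- Week 12: the recall starts no earlier than 77 − 28 = day 49, so it lies within period 1.
- Week 4: an early visit reaches back 28 − 21 = 7 days, into untreated time.

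**The case against.** The strongest reply is that the plan matches the recall as designed: on schedule the overlap is zero, and what remains is normal visit tolerance. That is right about the target dates. The windows are nevertheless set in the protocol itself, and a target with no slack turns ordinary lateness at week 12 into mixed recall.

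Second, the protocol does not say how GSRS scores will be compared or whether week 16 enters the comparison. Section 9 names weeks 12 and 24, and only for sCTx. An analysis plan could compare week 12 with week 24 and avoid the problem. This stands, and it makes the dilution conditional. The mixed recall exists in the data either way.

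Third, 5.1 prescribes each formulation for 12 weeks, so a 13th week on spare tablets is possible but not prescribed. This also stands. If a woman stopped at week 12 and waited for a late visit, however, those days would still not be days on the second formulation.

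Two stronger readings are tempting. A reader might infer that the no-shift rule by itself causes half of the recall to fall on the wrong drug. It does not: it explains 7 days, and the 14-day case also needs week 16 at its earliest permitted date. A reader might also infer that the GSRS comparison is biased toward no difference. The documents do not support that as a fact. It depends on week 16 being used, on recall days counting about equally, and on first-formulation symptoms late in period 1 resembling those in the score used for comparison.

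**Conclusion.** The point holds as a minor scheduling flaw in a secondary outcome. The protocol allows the week 16 recall to include up to 7 of 28 days on the first formulation from a late week 12 visit, and up to 14 if week 16 is also 7 days early. These bounds follow from the protocol alone, taking the switch as the day of dispensing.

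The group figures rest on assumed visit timing: a mean overlap of about 4% (SD 2 days) to 9% (even spread) of the recall. Any dilution of the brand versus generic contrast is of that order at this one visit, and only under the conditions named above. The week 12 and week 24 GSRS and the sCTx comparison are not touched. Nor are adverse events, for which 8.5 requires "dates of onset and resolution; severity; assessment of relatedness to investigational product and action taken".

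**What to change.** In 6.2.1 and 6.2.2 add an exception to the no-shift rule, for example: *Record the date of the first tablet of the second formulation. The week 16 visit, with its GSRS, takes place 28 to 35 days after that date. All other visits remain counted from Day 1.* No recall day at week 16 can then precede the second formulation. The 28-day floor is the essential part, since re-anchoring alone would leave up to 7 days of overlap.

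Leave week 24 where it is. Its recall already lies wholly in period 2, and moving it would shift the sCTx sample used for the primary outcome.

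The cost is one rule and one date field, with no extra visit, questionnaire or blood sample. The week 16 window narrows from 15 to 8 permitted days, and the visit may fall later than day 119: at the latest 91 + 6 + 35 = day 132. That is still before the earliest week 24 visit (day 161) and the start of its recall (day 133). The final visit and the total study duration do not change.
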